#### 2.5.3. Sample Size

To calculate the sample size necessary to achieve adequate statistical power in the evaluation of the program, the G*Power 3.1 program was used [66]. Two calculations were made for the sample size. The first calculation that was carried out for the pre-test and post-test analyses was made a priori for ANOVA analysis of repeated measures within–between interaction, with a mean Cohen effect size *f* = 0.25 [67] and α = 0.05, two groups with two temporal measures, correlation between the measures of 0.50, and sphericity of 1. With these assumptions, to achieve the acceptable minimum Cohen effect size of 0.80 [68] and obtain a statistical power of 0.80, the sample should consist of at least 34 participants. Although regarding the size of the control group, following a common knowledge rule in program evaluation, the control group should be composed of a minimum of (*n*/2) + 1—where *n* is the sample size of the group of participants—in this study, a minimum of 20 participants is established for the control group, with the objective of reaching the recommended size for the parametric tests [69].

The second sample calculation that was carried out for the follow-up analysis of the intervention group was performed a priori for the ANOVA analysis of repeated measures within factors, with a mean Cohen effect size *f* = 0.25 [67] and α = 0.05, a group with three temporal measures, correlation between the measures of 0.50, and sphericity of 1. With these assumptions, to achieve the acceptable minimum Cohen effect size of 0.80 [68] and obtain a statistical power of 0.80, the sample should be made up of at least 28 participants.

Among the analyses that were conducted, the most restrictive was the first calculation referring to pre-test and post-test measures of the intervention group and the control group; thus, we assume that the study sample must consist of at least 34 participants for the intervention group and 20 participants for the control group.

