The effectiveness of the MBSR-P intervention will be examined by performing two-way repeated measures ANOVA for each effectiveness dimension studied, with the group (0 = *control*, 1 = *intervention*) as the factor. Interaction effects will be examined. *R*^2^ will be computed as the effect size index, and will be evaluated according to the conventional levels of 0.01, 0.06, and 0.14 for the small, medium, and large effect size levels, respectively [67]. The corrected *R*^2^ will be calculated taking into account the within- and between-subjects errors [75]. In the event that the assumptions for these analyses are not fulfilled (e.g., if normality is violated and not able to be fixed by variable transformations), Wilcoxon’s non-parametric tests will be used as an alternative [74]. Mean and standard deviation will be provided for participants’ satisfaction, and for the implementation of information registered in the field diaries.

Figure 2 shows the steps that will be followed for quantitative data analysis.

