Once the category systems are created, the researchers will code separately and, subsequently, meet to discuss the categories and ascertain the degree of inter-observer reliability, which will be calculated by dividing the total number of agreements in the coding of all categories by the total number of agreements and disagreements in all categories [79]. Moreover, for the enumerative content analysis, the percentages of participants that have mentioned each category in their narrative will be calculated in order to obtain comparative data on which elements of the intervention are more frequently mentioned, and the areas in which the program has a greater impact on their daily lives. For the representation of these data, comparative graphs of the percentages of participants in each category will be made, and word clouds of the most common narratives in the categories will be provided. The word clouds will be created to identify the most frequent concepts that are talked about in the focus groups, organized by the previously identified categories and in a visual manner. To do so, a selection of the 50 most frequent words will be carried out, using as an inclusion criterion the length of the word (more than 3 letters). Secondly, words with the same root (e.g., parent and parenting) will be grouped under the same concept (e.g., “parenting”). Finally, we will eliminate linking and non-content words such as “between” or “element”. For the inductive thematic analysis, the two researchers will go back and forth through the data separately so as to identify possible themes. Later on, the proposed themes will be shared, and the researchers will discuss and not only agree on a set of themes, but also identify higher order themes and subthemes, define them in depth, and select quotes that represent those themes and subthemes.

To reach an adequate sample size that will enable us to carry out this content and thematic analysis using a representative sample, we will use the data saturation criteria. Taking into consideration the parameters proposed by Hennink et al. to estimate the sample size in focus groups, we will carry out between five and six focus groups so as to achieve both code and meaning saturation [80]. Code saturation is defined as the moment when no additional codes appear in the data, and meaning saturation is defined in terms of whether the qualitative data provide further information or insight on the codes [80].

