Moreover, by analyzing the narratives of the parents after the intervention, we expect to gain insight about the mechanisms involved in their processes of change during the intervention. First, from the mindfulness-based intervention approach, and based on the existing theoretical and empirical evidence on mediators, we expect non-judgmental mindful attention, self-nourishing attention, awareness of their parental roles, awareness of their own negative patterns of communications and thoughts, and the reduction in reactivity to be identified as the pillar elements that have prompted the changes associated with their participation in the program [6,85,86,87]. Additionally, considering the relevance of home practices for the intervention outcomes, we expect the continuous use of the techniques and strategies learned throughout the program to be considered as an important element for the maintenance of changes during and after the intervention [88]. Second, from the experiential methodology employed in the MBSR-P program, we expect that participants will highlight the relevance of focusing on their own experiences to build up their learning by remodeling their beliefs, knowledge, and abilities [41]. Third, the group format is expected to favor social learning, and to be reported by the participants in terms of modeling, cognitive insight, emotional expression, or interpersonal learning [89].

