### Appendix A.3. Field Diary

**Table A3 ijerph-18-10777-t0A3:** Questions from the field diaries.

1. Place where the session takes place	
2. Professional in charge of the group	
3. Which group is it?	
4. Session number	
5. Date	
6. Approximate length of the session	
7. Program activities developed during the session (indicate time)	
8. How was the atmosphere during the development of the session? Indicate whether there has been harmony between the participants during the development of the activities	1. Not adequate 2. Somehow adequate 3. Quite adequate 4. Very adequate
9. What is your general assessment of the sessions?	1-2-3-4-5-6-7-8-9-10
10. Any noticeable issues in the session? Strengths of the program, aspects of the program that have not worked well, or other observations about the course of the session, if there has been any modification in the planning…	
PARTICIPANTS (This information will be provided about every participant after each session)	
1. Participant identifier	Attendance (Yes/No) Level of participation 1. Low 2. Medium 3. High

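### MBSR-P is delivered in groups, but the ANOVA and both sample-size calculations treat parents as independent; if outcomes correlate within a group, the tests are anticonservative, most at the single-arm follow-up

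*Protocol article*

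**What the plan says.** Section 2.6.1 sets the method: "The effectiveness of the MBSR-P intervention will be examined by performing two-way repeated measures ANOVA". In full, it is a "two-way repeated measures ANOVA for each effectiveness dimension studied, with the group (0 = *control*, 1 = *intervention*) as the factor", and the section says that interaction effects will be examined. No other between-subject factor is named. Independence of observations is not among the assumptions listed for checking.

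Section 2.5.3 gives the first calculation as "ANOVA analysis of repeated measures within–between interaction, with a mean Cohen effect size *f* = 0.25 [67] and α = 0.05", for "two groups with two temporal measures, correlation between the measures of 0.50, and sphericity of 1", and concludes that to "obtain a statistical power of 0.80, the sample should consist of at least 34 participants". The second calculation covers the follow-up in the intervention group alone: a within-factor ANOVA with three measures and the same f, alpha, correlation and sphericity, giving 28. Neither has an ICC or a design effect. The adopted minimum is 34 intervention and 20 control parents.

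On delivery, sections 1.4 and 2.5.1 describe sharing and exercises within the group, and section 3.1 states that "the group format is expected to favor social learning". Controls come from the waiting list (section 2.4.2) and provide pre- and post-test data only (section 2.5.2). The field diary in Appendix A.3 asks "Which group is it", but the quantitative analysis makes no use of the answer.

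**The concern.** Parents in one programme group share the sessions, the discussions and the course of that particular group. If this moves their outcomes in the same direction, their changes are positively correlated, and the mean change of 34 treated parents is less precise than that of 34 independent ones. Controls have no such structure before post-test, so the design is partially nested: clustered in one arm and not in the other.

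An ANOVA without a group term understates the error variance of the mean change and rejects too often. In the two-arm comparison the ungrouped controls dilute this. At the 6-month follow-up there is no control arm, so the full design effect applies, and that analysis carries the claim in section 3.1 that changes are maintained.

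**Working it through.** **Reproducing the plan's figures.** Noncentral F with λ = f² × N × (measures)/(1 − ρ), f = 0.25, ρ = 0.50, sphericity 1.

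- Calculation 1 (two measures, df 1 and N − 2): λ = 0.0625 × 34 × 2/0.5 = 8.5; power is 0.807 at N = 34 and 0.795 at N = 33. Minimum 34, as stated.
- Calculation 2 (three measures, df 2 and 2(N − 1)): λ = 0.0625 × 28 × 3/0.5 = 10.5; power is 0.812 at N = 28 and 0.796 at N = 27. Minimum 28, as stated.

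Both formulas assume independent parents.

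**Number of groups.** The article does not state it. Section 2.2.3 places the discussion group in the programme's last session, and section 2.6.2 says "we will carry out between five and six focus groups so as to achieve both code and meaning saturation". That suggests five to six programme groups, or 34/6 = 5.7 to 34/5 = 6.8 parents each at the minimum sample. Section 2.5.1 gives 10 to 40 as typical for the original MBSR, so three groups (34/3 = 11.3 each) are shown as an alternative.

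**Design effect.** DE = 1 + (m − 1) × ICC, where m is group size and ICC is the within-group correlation of change. No ICC is given; 0.01, 0.05 and 0.10 are assumptions.

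For the two-arm contrast the variance ratio is (DE/34 + 1/20)/(1/34 + 1/20). With five groups and ICC 0.10, DE = 1 + 5.8 × 0.10 = 1.58, and the ratio is (0.0465 + 0.0500)/(0.0294 + 0.0500) = 1.215. The true standard error is then √1.215 = 1.10 times the one the ANOVA uses. In the single arm it is √1.58 = 1.26 times.

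**Type I error of the planned tests.** Simulated with 34 treated parents in groups and 20 independent controls. The follow-up test is the three-measure F-test with 2 numerator degrees of freedom, with the same ICC on both time contrasts.

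| Groups | ICC | DE | Two-arm interaction | Single-arm follow-up |
|---|---|---|---|---|
| 5-6 | 0.01 | 1.05-1.06 | about 5% | about 6% |
| 5-6 | 0.05 | 1.23-1.29 | about 6% | 9-10% |
| 5-6 | 0.10 | 1.47-1.58 | 7-8% | 13-15% |
| 3 | 0.01 | 1.10 | about 5.5% | about 7% |
| 3 | 0.05 | 1.52 | about 7% | about 14% |
| 3 | 0.10 | 2.03 | about 10% | about 23% |

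**Power, approximately, at five groups and ICC 0.10.** The 34 treated parents carry the information of 34/1.58 = 21.5. Power of the single-arm test with 34 parents falls from 0.89 to 0.69. The two-arm test with 34 + 20 falls from 0.94 to 0.89. The single-arm requirement of 28 becomes 28 × 1.58 = 44.2, so 45.

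**Which group term works.** A group effect that is constant over time cancels from every pre-post difference. In a generalised least squares check (34 treated in five groups, 20 controls, two measures, correlation 0.5, unit variance), the standard error of the arm-by-time interaction is 0.2818 whether the variance of the group intercept is 0, 0.05, 0.10 or 0.50. With a group-by-time variance of 0.05 it rises to 0.3154.

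**The case against.** The strongest reply is that the size of the problem is unknown. No ICC is given, a manualised programme may keep differences between groups small, and at ICC 0.01 with five to six groups the two-arm test is practically at its nominal level. The number and size of groups are inferred by dividing a minimum sample by a qualitative saturation target. The two-arm comparison also has slack, since 34 + 20 exceeds the required total of 34, and in a non-randomised study confounding is the larger threat. All of this stands, and it makes the finding conditional. It does not remove it: the article itself expects parents in a group to affect one another, section 2.5.3 applies no allowance, and the limitations in section 3.2 acknowledge the lack of randomisation but not clustering.

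A reader might infer that the reported p-values and confidence intervals will certainly be too optimistic. The documents do not support that. It depends on a materially positive ICC, and section 2.6.1 names F-tests and R², with no confidence intervals. A reader might also suspect correlation between two parents of the same child; the article neither plans nor excludes joint enrolment, so nothing is built on it here.

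Nor is this a detail that an article may leave to a fuller plan: the model and the power inputs are both spelled out.

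**Conclusion.** The concern holds in conditional form. The stated ANOVA and both sample-size calculations ignore a partially nested design that the article itself describes. If changes correlate within programme groups, the two-arm interaction test is mildly anticonservative and the single-arm follow-up test clearly more so. With five to six groups the error ranges from near nominal at ICC 0.01 to 7-8% (two-arm) and 13-15% (follow-up) at ICC 0.10; fewer, larger groups make it worse. These figures rest on assumed ICCs, an inferred number of groups, and the minimum sample of 34 and 20. The point should be corrected before analysis, chiefly for the sake of the follow-up claim.

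**What to change.** In section 2.6.1, replace the ANOVA with a partially nested mixed model that uses the group identifier already in the field diary. The programme-group random effect must act on change: either a group-by-time random effect in the repeated-measures model, or a group random intercept in a model of change scores or of baseline-adjusted post-test scores. It applies in the intervention arm only, with controls as singletons and Satterthwaite degrees of freedom. A group random intercept alone in the repeated-measures model would leave the interaction and the time contrasts uncorrected.

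Use the same approach for the 6-month contrasts and report the estimated ICC. In section 2.5.3, state the expected number and size of programme groups, and say that the 0.80 power behind N = 34 and N = 28 assumes independent parents and is lower under clustering.

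The change needs no new data, visits or participants. Its price is less favourable p-values and few degrees of freedom: five or six groups estimate a group variance poorly, which should be listed as a limitation.

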Moreover, we do not have enough information about the effectiveness of this intervention for families in vulnerable situations, such as parents with children with mental health disorders. It is necessary to provide evidence for the effectiveness of the MBSR with a positive parenting component, and to determine whether after their participation the parents managed to mitigate the negative consequences for parenting by taking into account their family circumstances. Knowing the effectiveness of this intervention for this type of population is of particular interest, considering the high levels of stress in these families [2], and that stress reduction is a central element of the MBSR, among other mindfulness-based modalities [13,18].

Finally, research on the implementation and effectiveness of mindfulness-based programs has predominantly involved the use of quantitative methodologies [43]. The combination of quantitative and qualitative techniques and strategies would enrich the evaluation of mindfulness-based programs, allowing consideration of the integral views of the participants, and providing a more complete representation of the complexities behind the learning, integration of practices in daily life, and the implementation process [44]. This will help to provide a better understanding of how the program works in the target population, and to enable it to be adapted and improved so that it is as beneficial as possible [36,42]. Along with this, satisfaction evaluations should be included regarding the core components of the program, in order to obtain the views of the participants so as to accommodate their needs and demands and optimize the process [45,46].

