#### 2.2.2. Effectiveness Measures

The effectiveness measures will be collected at pre-test, post-test, and follow-up. These measures are described as follows:

Stress. The first measure is related to the levels of perceived stress during the past month, which will be evaluated through the Perceived Stress Scale (PSS) [49,50]. This questionnaire contains 14 items (e.g., “In the last month, how often have you felt nervous or stressed?”). The scale of Likert responses ranges from 0 = *never* to 4 = *very often*, where 4 means the highest level of perceived stress. The instrument score is obtained from the mean of the scores, whose values range between 0 and 4. Research on the reliability and validity of this instrument shows internal consistency and validity, with a reliability value of α = 0.81.

Mindfulness. The second measure will be the evaluation of the levels of mindfulness and awareness in the present moment over a short period of time through the Mindfulness Attention Awareness Scale (MAAS) [51,52]. This instrument is composed of 15 items (e.g., “I do things quickly and hastily without paying much attention to what I am doing”), and uses a 6-point Likert scale, between 1 = *almost always* and 6 = *almost never*, where higher scores indicate a higher degree of mindfulness. The instrument score is obtained by calculating the mean of the scores, whose values range between 1 and 6. Research on the reliability and validity of this instrument has shown high internal consistency, with a Cronbach’s alpha of α = 0.88, and with significant values of criterion and discriminant validity.

Emotional Intelligence. The third measure is related to emotional intelligence, which will be assessed using the Emotional Quotient Inventory Short Form (EQi) [53,54,55]. This scale has 35 items (e.g., “When facing a problem, the first thing I do is stop and think”), which are divided into 4 subscales: intrapersonal intelligence, interpersonal intelligence, adaptability, and stress management. The response to the items is on a Likert-type scale, ranging from 1 = *very rarely true in me* to 5 = *very frequently true in me*. The score of the instrument is obtained from the means of the items belonging to each subscale, whose values range between 1 and 5. The reliability data of the instrument are acceptable in all subscales: 0.73 in the intrapersonal dimension, 0.78 in the interpersonal dimension, and 0.70 and 0.75 for adaptability and stress management, respectively.

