### 2.6. Data Analysis

#### 2.6.1. Quantitative Data

The analysis of the quantitative data will be carried out using the statistical program SPSS v-21 (IBM Corp., Armonk, NY, USA) [70]. Firstly, missing data at the level of the Likert scale questionnaires will be studied. Little’s MCAR test will be used to verify whether missing data per questionnaire are below 10%, which will mean that they are randomly distributed. If this assumption is met, it will also be verified whether missing data per item have a percentage below 5% and, if so, the data will be imputed through the SEM procedure using the expectation maximization (EM) algorithm from SPSS. For those cases with missing data at the questionnaire level, the cases will be discarded [71].

The distribution of the values will also be evaluated through asymmetry and kurtosis, and the presence of extreme cases in the variables studied will be examined by analyzing the interquartile ranges through stem and leaf graphs [72].

Moreover, other statistical assumptions for the parametric tests will be checked and reported (i.e., sphericity, normality, linearity, homogeneity, and absence of multicollinearity and singularity) [73]. If the sphericity assumption is not fulfilled, the *F*-test will be adjusted as an alternative for analysis with the Greenhouse–Geisser index, reducing the degrees of freedom associated with the *F* statistic of the ANOVA as a function of the corrective factor ε [74]. If normality violation occurs, parsimony transformations will be applied to correct the non-normal distributions [75]. If multicollinearity applies, composited factors will be computed for those involved variables.

The sociodemographic variables will be used to describe the samples, to control for them in the main analyses, and to achieve equivalence between the characteristics of the control group and those of the intervention group. Both descriptive and correlational analyses will be performed as preliminary analyses.

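### Effectiveness is judged on 11 to 15 unranked scores with no primary outcome, success rule or multiplicity control, while the sample size is calculated for one unnamed test at 0.05

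*Protocol article*

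**What the plan says.** Section 2.6.1 (Quantitative Data) sets the testing rule: a "two-way repeated measures ANOVA for each effectiveness dimension studied", with group as the factor and interaction effects examined. It states no significance level for these tests. It grades effect sizes as small, medium or large, but does not say what result would establish effectiveness.

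Section 2.2.2 (Effectiveness Measures) lists five instruments side by side. For the PSS, "The instrument score is obtained from the mean of the scores, whose values range between 0 and 4". The MAAS also has one mean score. The EQi and the GHQ are each scored as four subscale means, and no total is described. The MaaP has a general scale and four subscales.

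Section 2.5.3 (Sample Size) bases the pre-post calculation on an "ANOVA analysis of repeated measures within–between interaction, with a mean Cohen effect size" f of 0.25 and α = 0.05, with "two groups with two temporal measures, correlation between the measures of 0.50, and sphericity of 1". To "obtain a statistical power of 0.80, the sample should consist of at least 34 participants". The plan then settles on "at least 34 participants for the intervention group and 20 participants for the control group". It does not say which outcome the calculation concerns.

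Section 2.6.1 also contains this rule: "If multicollinearity applies, composited factors will be computed for those involved variables". It gives no threshold and does not say whether the variables are outcomes or covariates.

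**The concern.** Effectiveness is objective 2 in section 1.5, and section 3.1 expects change in all five areas without ranking them. When many scores are tested in parallel and none is designated in advance, a programme with no effect has a good chance of producing a significant interaction somewhere. The plan does not say how a reader should weigh one or two such results among a dozen or more. The stated power of 0.80 belongs to one test, while the analysis is a family of tests. At stake is whether a positive report could be distinguished from chance.

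**Working it through.** **1. Reproduce the plan's own figure.** For the within-between interaction, λ = f²·N·m/(1 − ρ), with df1 = (k − 1)(m − 1) and df2 = (N − k)(m − 1). With f = 0.25, N = 34, m = 2 measurements, ρ = 0.50 and k = 2 groups:

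- λ = 0.0625 × 34 × 2 / 0.5 = 8.5, with df 1 and 32.
- Power at α = 0.05 is 0.807. At N = 33 it is 0.795.

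So 34 reproduces as a total sample for one unadjusted test at 0.05. The planned 34 + 20 = 54 gives power 0.936 for that same single test, allowing for unequal groups.

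**2. Count the scores (section 2.2.2).**

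- PSS 1 + MAAS 1 + EQi 4 + GHQ 4 + MaaP 5 = 15.
- With the MaaP total only: 1 + 1 + 4 + 4 + 1 = 11.
- If each of the five areas were one test: 5. This fits the scoring poorly, because no total is described for the EQi or the GHQ.

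**3. Chance of at least one significant result when the programme has no effect.** There are two assumptions. The level is 0.05 per test, taken from section 2.5.3 because section 2.6.1 gives none. The correlation between outcomes is 0 to 0.7, because the article gives no value. For independent tests the chance in either direction is 1 − 0.95^k; for k = 15 it is 1 − 0.95^15 = 0.537. With two groups and two time points the interaction has one degree of freedom, so half of the 0.05 lies in the favourable direction. The favourable-only chance is then 1 − 0.975^k; for k = 15 it is 0.316. Correlated cases come from 400,000 simulated draws of equally correlated normal test statistics.

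| Scores | Direction | r = 0 | r = 0.3 | r = 0.5 | r = 0.7 |
|---|---|---|---|---|---|
| 15 | either | 53.7% | 45.8% | 36.0% | 25.6% |
| 15 | favourable | 31.6% | 23.5% | 18.1% | 12.9% |
| 11 | either | 43.1% | 37.5% | 30.3% | 22.3% |
| 11 | favourable | 24.3% | 19.1% | 15.2% | 11.2% |
| 5 | either | 22.6% | 20.9% | 18.4% | 14.9% |
| 5 | favourable | 11.9% | 10.5% | 9.1% | 7.4% |

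A single two-sided test would give 5% and 2.5% respectively. The count takes one pre-post interaction per score; the three-time-point follow-up analysis of the intervention group would add more.

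**4. What the remedies do to power at f = 0.25.** Bonferroni over 15 scores (0.05/15 = 0.0033 each) brings the familywise error to 4.9% if the tests are independent, but power per test falls to about 0.42 at N = 34 in equal groups, or 0.68 at 34 + 20. One designated primary outcome at 0.05 keeps the values in step 1.

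**The case against.** The strongest reply has four parts.

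- **No any-one-wins rule is written down.** Section 2.6.1 examines interactions by dimension and grades effect sizes. A reader might infer that an ineffective programme has a 26 to 54% chance of being declared effective. The documents do not support that: those figures include significant results showing harm, and no passage says that one significant result suffices. The favourable-direction figures are the relevant ones for a mistaken claim of benefit, and they too describe only the chance of having such a result to report.
- **The count and the level are inferred.** The term for what is tested is not defined, and section 2.2.2 numbers five measures. Reporting a score range for the MaaP total and subscales does not prove that all five will be tested. This stands, and it is why a range of counts is shown. Even five tests exceed the single-test rate.
- **Multiplicity detail may sit in a fuller plan.** This is fair for the choice of adjustment method. But the article fixes the testing rule, the fallbacks for failed assumptions, and a sample size for one test. The outcome behind that sample size should be named here.
- **The composite rule may concern covariates.** A reader might infer that it lets the data choose the endpoints. The text does not say that it covers outcomes, section 2.6.1 also plans to control for sociodemographic variables, and merging outcomes would reduce the number of tests. What stands is only that its scope is unstated and that separate univariate ANOVAs do not need uncorrelated outcomes.

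**Conclusion.** The concern holds in this form: the plan tests 11 to 15 unranked scores for its effectiveness objective, with no primary outcome, success rule or multiplicity control, and its power statement applies to one unnamed test. For an ineffective programme, the chance of at least one significant interaction is about 26 to 54% in either direction and 13 to 32% in the favourable direction with 15 scores, and 22 to 43% and 11 to 24% with 11. On the most lenient reading, five tests, it is 15 to 23% and 7 to 12%. The upper ends assume independent outcomes and the lower ends a correlation of 0.7; neither comes from the article, and 0.05 per test is carried over from the sample-size section. The size depends on these assumptions, but every case examined is above the single-test rate.

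**What to change.** Before the data are analysed:

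- Name one primary outcome. The PSS pre-to-post group × time interaction is the natural choice: section 1.3 gives stress reduction as the main objective of MBSR, and section 1.4 says that "stress reduction is a central element of the MBSR". Because the programme adds a parenting component, the authors could argue for the MaaP instead; what matters is that one outcome is fixed in advance.
- Test it at 0.05 and base the effectiveness conclusion on it. The single-test calculation in section 2.5.3 then applies to a named outcome.
- List the remaining scores explicitly, saying whether the MaaP total, its subscales or both are tested. Treat them as one secondary family with Holm adjustment (14 scores if all 15 are kept, so the smallest p-value faces 0.05/14 = 0.0036), and report 95% confidence intervals for all.
- State that the multicollinearity composite rule applies to covariates and not to outcomes.

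This costs wording only and calls for no extra participants for the primary test. The downside is a stricter threshold for the secondary outcomes.
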